### Study variables

In this study, the designed interventions will be considered as an independent variable, and lifestyle will be considered as a dependent variable.

### Data collection method

The lifestyle questionnaire, which is completed by the interview method, is the tool used in the quantitative phase of this research. The questionnaire includes 70 questions, which designed to evaluate various aspects of lifestyle (e.g. physical health, exercise, weight and nutrition control, disease prevention, psychological health, spiritual health, social health, avoidance of medicines and drugs, prevention of accidents and environmental health). The scoring scale is in Likert format. The response range is assessed based on frequency of action. The frequency of action is measured as “always, often, sometimes, very rare, rarely”. The total score for each aspect comes from the sum of scores.

### The implementation method of the quantitative phase

The researcher will implement the designed intervention after obtaining a permit from the Ethics Committee of the Isfahan University of Medical Sciences, and performing the necessary coordination with the officials of the specified centers. In this way, the researcher first discuss the research objectives by attending predetermined referral centers; then, through the available sampling method to the research units having criteria for entering the study, and, if they agree and give informed consent, the person enters in the study. Life style of participants will be considered as a proposed outcome.

### Data analysis

The collected data will be analyzed using descriptive statistical methods (mean, standard deviation and frequency) and inferential statistics (independent t, paired t-test, Chi-square, Fisher’s exact test, Wilcoxon and Mann-Whitney) and by using SPSS 20 software. If there are confounding variables, ANCOVA will be used to modify them.

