### Sample size

With a confidence level of 95% and a statistical power of 90%, along with considering the standard deviation of lifestyle score, which is equal to P_1_ = 0.87 and P_2_ = 0.69 and with EFFECT SIZE of 0.18, the sample size is considered to be 43 in each group.

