### Sampling method

The sampling of this part of research is carried out by available and non-probabilistic sampling method. Researcher by referring to postpartum wards of hospitals affiliated to Isfahan University of Medical Sciences on consecutive days selects 86 women with preeclampsia and having the criteria for entering the study in the easy method. Subsequently, subjects are assigned to the intervention and control groups by means of the RANDOM ALLOCATION software.

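### ANCOVA is conditional on finding confounders, so a randomised comparison has no fixed adjustment for the baseline lifestyle score that the paired tests imply

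*Protocol article*

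**What the plan says.** The inferential plan in the Data analysis section of the protocol article is one list followed by one conditional sentence. The list is "inferential statistics (independent t, paired t-test, Chi-square, Fisher’s exact test, Wilcoxon and Mann-Whitney". The condition is "If there are confounding variables, ANCOVA will be used to modify them". The section does not say which variables count as confounders, how one would be recognised, which test decides the effect of the programme, or whether final or change scores are compared.

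Under Sampling method, "subjects are assigned to the intervention and control groups by means of the RANDOM ALLOCATION software". Study variables names lifestyle as the only dependent variable. Data collection method describes the questionnaire but gives no measurement times.

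Under Sample size, the plan claims "a statistical power of 90" per cent and continues: "with EFFECT SIZE of 0.18, the sample size is considered to be 43 in each group".

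**The concern.** When allocation is random, adjusting for a baseline variable serves mainly to gain precision. A strong predictor of the outcome should therefore be adjusted for by prior decision, whether or not the groups happen to differ on it. A rule that adjusts only if confounding is found makes the model depend on the observed data. With no covariate and no trigger named, the analyst could see both the adjusted and the unadjusted result before choosing.

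The obvious covariate here is the lifestyle score at entry. Its existence is an inference: a paired t or Wilcoxon test, listed beside the two-sample tests in a study with one dependent variable, has no evident use without a before and an after score. If that score is collected, the plan as written does not put it into the group comparison by default. At stake are power in a study of 86 women and the reliability of the nominal 5% error rate.

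**Working it through.** **Inputs.** From the article: 43 per group, 86 in total, 95% confidence (taken as two-sided 5%), 90% power. Not in the article, so assumed: the correlation r between baseline and follow-up score (0.3, 0.5, 0.7) and, for one illustration, a true effect of 0.5 SD.

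**Step 1: the plan's own figure.** The Sample size section describes "the standard deviation of lifestyle score, which is equal to P_1_ = 0.87 and P_2_ = 0.69" and an effect size of 0.18, which equals 0.87 − 0.69. At 90% power, two-sided:

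- Read as two proportions, 110 per group are needed.
- Read as two means with difference 0.18 and SDs 0.87 and 0.69, n = (0.87² + 0.69²)(1.960 + 1.282)² / 0.18² ≈ 400 per group.
- Read as a standardised difference of 0.18, 649 per group are needed.

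None of these gives 43. With 43 per group the power is 52%, 18% and 13% respectively. This is a separate problem. It matters here only because the stated 90% is not a secure starting point, so two starting points are used below.

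**Step 2: gain from always adjusting.** ANCOVA on the baseline score multiplies the residual variance by 1 − r², so a standardised effect d acts like d/√(1 − r²).

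*Start A, the unadjusted test has the stated 90% power.* The implied effect is (1.960 + 1.282) × √(2/43) = 0.70 SD. Power is by normal approximation.

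*Start B, an assumed 0.5 SD effect.* Power is from the t distribution with 43 per group.

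| r | 1 − r² | Per group under ANCOVA to match 43 unadjusted | Power, start A | Power, start B |
|---|---|---|---|---|
| 0 | 1.00 | 43 | 90% | 63.0% |
| 0.3 | 0.91 | 40 | 92.5% | 67.1% |
| 0.5 | 0.75 | 33 | 96.3% | 75.4% |
| 0.7 | 0.51 | 22 | 99.5% | 89.4% |

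**Step 3: if change scores were compared instead.** The article does not exclude this. With equal variances, the change score has variance 2(1 − r) times that of the final score. The ratio of ANCOVA variance to change-score variance is (1 − r²)/[2(1 − r)] = (1 + r)/2, which is below 1 for any r below 1. For 0.5 SD, change-score power is 63% at r = 0.5 and 84% at r = 0.7, against 75% and 89% for ANCOVA.

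**Step 4: type I error.** This was simulated with 20,000 trials per value of r, 43 per group, normal scores and no programme effect.

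| Strategy | r = 0.3 | r = 0.5 | r = 0.7 |
|---|---|---|---|
| Always t | 4.9% | 5.1% | 5.0% |
| Always ANCOVA | 4.9% | 5.1% | 5.0% |
| ANCOVA only if a baseline test has p < 0.05, otherwise t | 4.7% | 4.4% | 3.6% |
| Better of t and ANCOVA | 6.3% | 7.5% | 8.2% |
| Best of t, Mann-Whitney and ANCOVA | 7.2% | 8.3% | 9.0% |

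A mechanical trigger is therefore slightly conservative. Inflation appears only when the analyst is free to choose, which the present wording allows.

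**The case against.** Several stronger readings are tempting, and the article does not support them.

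- *That baseline lifestyle is known to be measured and the primary test known to be an unadjusted t or Mann-Whitney.* Neither is stated. The first is a strong inference from the paired tests. The second is the natural reading, but no test is tied to the primary comparison. Step 3 shows that ANCOVA still gains if change scores were meant, though by less when r is high.
- *That every baseline difference must be chance.* This holds for the groups as allocated. The Exclusion criteria, however, remove women who receive too little of the intervention, which can only be known after allocation. Differences between the groups as analysed need not be chance alone.
- *That the conditional rule inflates type I error by itself.* It does not, as the fixed-trigger row in Step 4 shows.
- *That the paired tests will be used to judge effectiveness.* Nothing says so. If both groups changed equally, the chance of significance in the programme arm alone would be p(1 − p), where p is the power of each paired test. That runs from about 3% to its maximum of 25% for changes of 0.1 to 0.6 SD. It describes a possible misreading of results, not an error in the plan.

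It can also be said that covariates and a trigger may stand in an analysis plan that is not shown. That is fair as to detail, and their absence alone would be no finding. But the article does state the condition itself, and more detail on how to apply it would not make it a good rule for a randomised comparison. Finally, at the stated 90% power and r = 0.3 the gain is only 2.5 points. That stands: the benefit may be small.

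**Conclusion.** The point holds in a limited form. Making ANCOVA conditional on finding confounders is the wrong rule for randomly allocated groups, and it leaves the choice of model open until the data are seen. If a baseline lifestyle score is collected, always adjusting for it adds 2.5 to 9.5 percentage points of power from a 90% start, or about 4 to 26 points from a 63% start, for r between 0.3 and 0.7. Both r and the 0.5 SD effect are assumptions. The direction is firm for any appreciable correlation, but the size cannot be fixed from the article. A free choice between t and ANCOVA would take type I error to about 6% to 8%. This does not invalidate the trial, but the sentence should be changed before analysis.

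**What to change.** State one primary analysis: an ANCOVA of the follow-up lifestyle score on allocated group and baseline lifestyle score, fitted whatever the observed balance, with the adjusted difference and its 95% confidence interval reported. Delete the condition about confounding variables. Keep the independent t and Mann-Whitney tests as sensitivity analyses and the paired t and Wilcoxon tests as description only. State explicitly that lifestyle is measured at baseline and at follow-up.

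If the baseline score is already collected, as the paired tests imply, the cost is rewording only: ANCOVA and the software are already in the plan. If it is not collected, one further administration of the questionnaire at entry is needed.

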## Discussion

Various studies suggest that women with preeclampsia history need serious follow-up to manage the risk factors of chronic and cardiovascular diseases [8–10, 17, 18, 37–41]. Shortage in awareness of maternal care providers and lack of comprehensive instructions are the main reasons for neglecting them [11, 33, 34, 42, 43]. Further, missing evidence of cost-efficient post-preeclamptic follow-up strategies along with possible differences in clinical recommendations converge to indicate the demand for further research to improve and optimize prevention approaches [5].

Researchers also support studies on applying postpartum lifestyle interventions on women who have preeclampsia history as a strategy to prevent future cardiovascular disease and promote their health [9, 33, 44].

Due to importance of well-designed follow-up plan for women suffering preeclampsia [31], the present study aims to design and conduct a comperhensive postpartum follow-up health care program for participants. The program will be designed in a framework to provide regular and structured follow-up to reduce postpartum morbidity and improve women’s health through lifestyle change by evaluating and controlling the risk factors, which can lead to improving quality of life and longer life by preventing chronic diseases, as well as reducing the health care costs. This type of integrated intervention can be considered a significant strategy to reduce risk costs effectively. As a result, it is expected that the success of providing such a program, to some extent, could prevent health problems among these women who might be neglected due to high burden of disease. If this program is effective, it could be included in the postpartum health care guidelines. The results of the study will be provided to maternal health policy-makers in the health system.

## Abbreviations

AHA: American Heart Association
HELLP: H: hemolysis EL: elevated liver enzyme LP: low platelet
